## Abstract

**Background:**

Early-onset pre-eclampsia with raised blood pressure and protein in the urine before 34 weeks’ gestation is one of the leading causes of maternal deaths in the UK. The benefits to the child from prolonging the pregnancy need to be balanced against the risk of maternal deterioration. Accurate prediction models of risks are needed to plan management.

**Methods:**

We aim to undertake a multicentre prospective cohort study (Prediction of Risks in Early onset Pre-eclampsia (PREP)) to develop clinical prediction models in women with early-onset pre-eclampsia, for risk of adverse maternal outcomes by 48 h and by discharge. We will externally validate the models in two independent cohorts with 634 and 216 women. In the secondary analyses, we will assess risk of adverse fetal and neonatal outcomes at birth and by discharge.

**Discussion:**

The PREP study will quantify the risk of maternal complications at various time points and provide individualised estimates of overall risk in women with early-onset pre-eclampsia to plan the management.

**Trial registration:**

ISRCTN registry, ISRCTN40384046

## Background

Pre-eclampsia is a multisystem disorder in pregnancy associated with hypertension and proteinuria [1–3] and occurs before 34 weeks in 1% of women, so called early-onset pre-eclampsia [4, 5]. In the UK, hypertensive disease in pregnancy remains a leading cause of direct maternal deaths and contributes to about 20% of all stillbirths [6].

With an increased risk of maternal complications and 20-fold higher maternal mortality, early-onset pre-eclampsia is considered to be pathophysiologically different from the late-onset disease [7–9]. The only known cure is delivery of the baby and placenta. However, fetal and neonatal benefits from delaying the pregnancy need to be balanced against the risk of multisystem dysfunction in the mother.

Although the proportion of women with early-onset pre-eclampsia is only 1% of all pregnancies, the complexity of the treatment gives rise to large health care costs [4, 5]. Women are often admitted to tertiary care, and with a third experiencing complications, a stay in an intensive care facility may become necessary [10]. Infants also have longer stays in intensive care facilities for management of complications such as lifelong handicaps arising as a result of prematurity.

One of the key recommendations in the last CEMACH (Confidential Enquiries into Maternal and Child Health) (now known as Centre for Maternal and Child Enquiries (CMACE)) report is the need to adopt an early warning system to help in the timely recognition, referral and treatment of women who have or are developing critical conditions [6]. Early identification of mothers with early-onset pre-eclampsia at risk of complications, and their risks for these at various time points after diagnosis, will allow clinicians to make decisions on commencing interventions such as administration of steroids and, if needed, in utero transfer to a tertiary unit. In mothers considered to be of low risk, they can be monitored as an outpatient, and delivery may be delayed to lower the risk of perinatal complications from prematurity.

We aim to develop prediction models to quantify the overall risk of adverse maternal outcomes in women with early-onset pre-eclampsia and at various time points after diagnosis.

## Methods/design

The Prediction of Risks in Early onset Pre-eclampsia (PREP) study will be developed using existing recommendations on prognostic research model development and validation [11–13] and reported in line with the Transparent Reporting of a multivariable prediction model for Individual Prognosis Or Diagnosis (TRIPOD) statement [14]. Ethical approval for the study was received from the NRES Committee West Midlands (approval number 11/WM/0248), and the study was registered on ISRCTN registry as per the requirements set out by the World Health Organization (WHO) International Clinical Trials Registry Platform (ICTRP) and the International Committee of Medical Journal Editors (ICMJE) [15] guidelines with registration number ISRCTN40384046 [16].

### Objectives

The primary objectives are to develop and internally validate a prediction model in women admitted with early-onset pre-eclampsia from 20 weeks and 0 day to 33 weeks and 6 days of gestation, for assessment of the risk of adverse maternal outcomes at 48 h and by discharge. The 48 h of time interval was chosen to reflect the time recommended for delivery after administration of steroids to lower risks of respiratory distress in newborns. This time period is also considered to be the optimal duration to make decisions on timing and place of delivery and consider in utero transfer to a tertiary care unit if needed. The model will be externally validated in two independent datasets of patients with a diagnosis of early-onset pre-eclampsia. Our secondary objective is to assess the risk of adverse fetal and neonatal outcomes at birth and at any time until discharge.

### Study design and conduct

PREP is a prospective, multicentre, observational cohort study involving secondary and tertiary care obstetric units in England and Wales. All consecutive women with a suspected or confirmed diagnosis of pre-eclampsia before 34 weeks of gestation will be approached to take part in the study by research midwives and clinicians in antenatal clinics, wards, day assessment units and delivery suites. Clinicians managing the women will be requested to complete the Clinicians Management Plan at baseline to assess the reasons for planned management. The predictors evaluated in the PREP prediction model are routinely performed as part of standard clinical practice in women admitted with early-onset pre-eclampsia. The PREP study does not influence the management of these patients.

### Inclusion criteria

Women aged 16 years or over and a diagnosis of new-onset or superimposed pre-eclampsia at gestational age between 20 + 0 and 33 + 6 weeks will be considered for inclusion in the study. Women with a diagnosis of HELLP (haemolysis, elevated liver enzymes, low platelets) syndrome and those with one episode of eclamptic seizures without hypertension or proteinuria will be considered for inclusion. All women will be required to provide written informed consent and must be capable of understanding the information provided. The definitions for the diagnosis of pre-eclampsia are provided in Table 1.

**Table 1 Tab1:** Definition of the inclusion criteria for recruitment into the PREP study

Condition	Definition
New-onset pre-eclampsia	New-onset hypertension (systolic BP ≥140 mmHg or diastolic BP ≥90 mmHg on 2 occasions 4–6 h apart in women) after 20 weeks of pregnancy and new-onset proteinuria (≥2+ in urine dipstick or PCR of greater than 30 mg/mmol or 300 mg of protein excretion in 24 h) [37]
Suspected pre-eclampsia	New-onset hypertension (systolic BP ≥140 mmHg or diastolic BP ≥90 mmHg on 2 occasions 4–6 h apart in women) after 20 weeks of pregnancy and 1+ proteinuria on urine dipstick
Superimposed pre-eclampsia	
- In women with chronic hypertension and no proteinuria before 20 weeks’ gestation	New-onset proteinuria (as defined previously)
- In women with significant proteinuria before 20 weeks’ gestation	Elevated serum alanine aminotransferase concentration (>70 U/L) or worsening hypertension (either 2 diastolic BP of at least 110 mmHg 4 h apart or 1 diastolic measurement of at least 110 mmHg if the woman had been treated with an anti-hypertensive drug), plus one of the following: increasing proteinuria, persistent severe headaches or epigastric pain
HELLP syndrome	Haemolysis, elevated liver enzymes, and low platelets syndrome: presence of haemolysis based on examination of the peripheral smear, elevated indirect bilirubin levels or low serum haptoglobin levels in association with significant elevation in liver enzymes and a platelet count below 100,000/mm^3^ after ruling out other causes of haemolysis and thrombocytopenia
1 episode of eclamptic seizures without hypertension or proteinuria	Other neurological conditions of seizures have been excluded

### Exclusion criteria

Women will be excluded if any of the outcomes (including recurrent eclamptic seizures) occurs prior to testing or if informed consent could not be obtained on time or if the mother does not have a good understanding of spoken and written English and a translator is unavailable.

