### Outcome measures

The primary outcome is a composite adverse maternal outcome including maternal neurological, haematological, cardiorespiratory, hepatic and renal complications and death. We prioritised the outcomes for clinical importance using a Delphi survey of researchers and clinicians. Prior to the analysis, after discussion with the independent Study Steering (SSC) and Data Monitoring (DMC) Committees, we included delivery before 34 weeks as a component of maternal composite outcome to minimise bias due to treatment paradox [23]. The secondary outcome is a composite adverse fetal outcome (Table 3).

**Table 3 Tab3:** Components of the maternal and fetal composite outcomes

Outcome	Definition
Maternal outcomes	
Mortality	Maternal death at any time in pregnancy after delivery until discharge
Hepatic dysfunction	INR >1.2 indicative of DIC in the absence of treatment with warfarin. (DIC is defined as having both abnormal bleeding and consumptive coagulopathy (i.e. low platelets, abnormal peripheral blood film, or one or more of the following: increased INR, increased PTT, low fibrinogen, of increased fibrin degradation products that are outside normal non-pregnancy ranges).)
Hepatic haematoma or rupture	Blood collection under the hepatic capsule as confirmed by ultrasound or laparotomy
Glasgow coma score <13	From the GCS scoring system [39]
Stroke	Acute neurological event with deficits lasting longer than 48 h
Cortical blindness	Loss of visual acuity in the presence of intact papillary response to light
RIND	Cerebral ischaemia lasting longer than 24 h but less than 48 h revealed through clinical examination
Retinal detachment	Separation of the inner layers of the retina from the underlying RPE (choroid) and is diagnosed by ophthalmological examination
Acute renal insufficiency	For women with an underlying history of renal disease: defined as creatinine >200 μM; for patients with no underlying renal disease: defined as creatinine >150 μM
Dialysis	Including haemodialysis and peritoneal dialysis
Transfusion of blood products	Includes transfusion of any units of blood products: FFP, platelets, RBCs, cryo or whole blood
Positive ionotropic support	The use of vasopressors to maintain a systolic blood pressure >90 mmHg or mean arterial pressure >70 mmHg

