Myocardial ischaemia/infarction	ECG changes (ST segment elevation or depression) without enzyme changes and/or any one of the following: (1) development of new pathologic Q waves on serial ECGs. The patient may or may not remember previous symptoms. Biochemical markers of myocardial necrosis may have normalised, depending on the length of time that has passed since the infarct developed. (2) Pathological findings of an acute, healed or healing MI. (3) Typical rise and gradual fall (troponin) or more rapid rise and fall (CK-MB) of biochemical markers of myocardial necrosis with at least one of the following: (a) ischaemic symptoms; (b) development of pathologic Q waves on the ECG; (c) ECG changes indicative of ischaemia (ST segment elevation or depression) or (d) coronary artery intervention (e.g. coronary angioplasty)
Require >50% oxygen for greater than 1 h	Oxygen given at greater than 50% concentration based on local criteria for longer than 1 h
Intubation other than for caesarean section	Intubation maybe by ventilation, electrical impedance tomography or continuous positive airway pressure
Pulmonary oedema	Clinical diagnosis with x-ray confirmation or requirement of diuretic treatment and SaO_2_ <94%
Postpartum haemorrhage	>1 L of blood loss after delivery
Early preterm delivery	Delivery at gestational age of less than 34 weeks
Fetal outcomes	
Perinatal or infant mortality	Death of a fetus or neonate. Infant mortality is the death of a child less than 1 year of age
Bronchopulmonary dysplasia	Oxygen requirement at 36 weeks’ corrected gestation unrelated to an acute respiratory episode
Necrotising enterocolitis including only Bell’s stage 2 or 3	Evidence of pneumotosis intestinalis on abdominal x-ray and/or surgical intervention
Grade III/IV intraventricular haemorrhage	Bleeding into the brain’s ventricular system, where the ventricles are enlarged by the accumulated blood or bleeding extends into the brain tissue around the ventricles
Cystic periventricular leukomalacia	Softening and necrosis in the hemispheric white matter in newborns that may result from impaired perfusion at the interface between the ventriculopetal and ventriculofugal arteries
Stage 3–5 retinopathy of prematurity	Abnormal blood vessel development in the retina of the eye, where blood vessel growth is severely abnormal, where there is a partially or totally detached retina

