Hypoxic ischaemic encephalopathy	Apgar score ≤5 at 10 min and/or pH 7.00 in the first 60 min of life and/or base deficit ≥−16 in the first 60 min associated with an abnormal consciousness level (lethargy, stupor or coma) and seizures and/or poor/weak suck and/or hypotonia and/or abnormal reflexes

Adapted from the PIERS study

*INR* international normalised ratio, *DIC* disseminated intravascular coagulation, *PTT* partial thromboplastin time, *GCS* Glasgow Coma Scale, *RIND* reversible ischaemic neurologic deficit, *RPE* retinal pigment epithelium, *FFP* fresh frozen plasma, *RBCs* red blood cells, *cryo* cryoprecipitate, *ECG* electrocardiography

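### The exclusion rule treats recurrent eclamptic seizures as a study outcome, but the maternal composite in Table 3 has no seizure component

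*Protocol article*

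**What the plan says.** Four parts of the protocol article bear on this.

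- **Inclusion criteria.** A single eclamptic episode can be an entry condition: "those with one episode of eclamptic seizures without hypertension or proteinuria will be considered for inclusion".
- **Exclusion criteria.** "Women will be excluded if any of the outcomes (including recurrent eclamptic seizures) occurs prior to testing". Recurrent seizures are given as an example of the outcomes.
- **Outcome measures and Table 3.** The text defines the primary outcome by organ system: "The primary outcome is a composite adverse maternal outcome including maternal neurological, haematological, cardiorespiratory, hepatic and renal complications and death". Table 3, titled "Components of the maternal and fetal composite outcomes", then lists and defines the events that count. Its rows include "Glasgow coma score <13", stroke ("Acute neurological event with deficits lasting longer than 48 h") and early preterm delivery ("Delivery at gestational age of less than 34 weeks").
- **Statistical analysis.** One survival model covers time points up to 34 weeks, including 48 h after admission, and one logistic model covers outcome by discharge. Failure in the survival model is an adverse outcome or a delivery that precedes 34 weeks.

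**The concern.** A prediction model needs one event definition, used twice: to remove women who have already had the event, and to classify those who have it later. Here the two uses disagree. The exclusion rule regards recurrent eclamptic seizures as the event, whereas the component list does not.

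At stake is who has the primary outcome, and when. Both models rest on the same composite, and so does the planned validation in PETRA and PIERS. Two people classifying the same woman could reach different answers, depending on which section they follow.

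**Working it through.** The point is a comparison of texts; the plan has no figure to reproduce.

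1. **Is seizure a maternal component?** The maternal rows of Table 3 are: mortality; hepatic dysfunction; hepatic haematoma or rupture; GCS below 13; stroke; cortical blindness; RIND; retinal detachment; acute renal insufficiency; dialysis; transfusion; inotropic support; myocardial ischaemia or infarction; more than 50% oxygen for over 1 h; intubation; pulmonary oedema; postpartum haemorrhage; early preterm delivery. That is 18 rows, none of them eclampsia or seizure. The table's only mention of seizures is in the neonatal definition of hypoxic ischaemic encephalopathy: "associated with an abnormal consciousness level (lethargy, stupor or coma) and seizures".

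2. **Does another section supply it?** The Outcome measures text names neurological complications only as a class, and Table 3 says which of them count. The survival failure event refers back to the adverse outcome and adds only early delivery.

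3. **What happens to each woman under the text as written?**
   - *Recurrent seizures before testing:* excluded, as having had an outcome.
   - *Recurrent seizures after testing, delivery before 34 weeks:* an event in the discharge model, through the delivery row. In the survival model, if no other row is met earlier, the failure time is the delivery and not the seizure. If the seizure falls inside 48 h and the delivery outside, she is not a failure at 48 h.
   - *Recurrent seizures after testing, delivery at or after 34 weeks, another row met (for example GCS below 13, intubation, stroke, death):* an event in the discharge model, through that row.
   - *Recurrent seizures after testing, delivery at or after 34 weeks, no other row met:* event-free in the discharge model. If the seizures came before 34 weeks, she is not a failure in the survival model either.
   - *First seizure after testing in a woman with none at entry:* not addressed. The exclusion rule speaks only of recurrent seizures and Table 3 is silent, so she is classified by the other rows, as in the three cases above.

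4. **Can the effect be sized?** No. That would need the rate of seizures after baseline among women who meet no other row, or meet one only later, and the article gives no eclampsia rate.

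**The case against.** The strongest reply is that the delivery component absorbs most of the problem. Every woman enters by 33+6 weeks, the Background describes delivery as the only known cure, and delivery before 34 weeks is itself an event. A woman who seizes and delivers before 34 weeks, in either order, is already counted in the discharge model. This stands, and it probably keeps the number of misclassified women low. It does not cover delivery at or after 34 weeks with no other row, and it does not correct the event time in the survival model.

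It could also be said that a journal article condenses its protocol. That does not explain the mismatch, because Table 3 is presented as the component list, defines even rare events in detail, and conflicts with something the article itself states.

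Three stronger readings are tempting, and the article does not support them.

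- *Every woman with a seizure after testing is scored as event-free.* This is wrong, because she may enter through one of the other rows.
- *The share of lost events can be quoted.* A reader might assume that 1–3% of women seize with no other component and set this against the initial plan: 10 predictors × 10 events = 100 events, and 100 / 0.20 = 500 women, so 5–15 missed events, or 5–15%. The rate has no source in the article. The comparator is also superseded: the plan now has 22 candidate predictors, which at about 10 events each implies 22 × 10 = 220 events. Against that number, the same 5–15 would be 5/220 = 2.3% to 15/220 = 6.8%. None of these percentages is an estimate from the article.
- *Predictor effects are biased toward the null.* Clonus, reflexes and headache or visual symptoms are plausibly related to seizure, so distortion is possible, but no direction can be shown. This applies especially to magnesium sulphate, which the Discussion enters as a treatment variable to account for management.

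**Conclusion.** The inconsistency is real: the exclusion rule names recurrent eclamptic seizures as an outcome, Table 3 does not contain them, and nothing else in the article settles which is meant. A seizure after testing therefore does not count in its own right. Two kinds of women are affected: those who deliver at or after 34 weeks and meet no other row, and those whose seizure precedes a delivery before 34 weeks, where the event may be timed too late for the 48 h prediction.

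The number of women is probably limited by the early-delivery component, and neither the size nor the direction of any bias can be calculated from the article. The conclusion rests only on reading Table 3 as the full component list, which is how the article presents it. The point deserves correction because it concerns the definition of the primary outcome, not because a large effect has been shown.

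**What to change.** Reconcile the Inclusion criteria, the Exclusion criteria and Table 3 before outcomes are classified, in one of two ways.

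- **If seizure is meant to be an outcome:** add an eclamptic seizure row to Table 3. It should cover at least the recurrent seizures named in the exclusion rule, and say explicitly whether a first seizure after baseline counts in a woman who had none at entry. Counting a first seizure goes beyond the exclusion rule's wording and adds to a list prioritised by Delphi survey, so it should be stated as a decision.
- **If seizure is not meant to be an outcome:** reword the Exclusion criteria so that recurrent seizures before testing are a separate exclusion and not an example of the outcomes. Simply deleting the parenthesis would change who is eligible without saying so.

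The cost is one table row or one reworded phrase. The first option also needs confirmation that seizures after baseline are recorded through to discharge; the eligibility check alone does not show this.

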### Candidate variables for inclusion in the model

Candidate predictor variables will be obtained from patient demographic characteristics and from clinical assessment including clinical history, examination and investigations. The predictors will be clearly defined and standardised to ensure reproducibility and enhance generalisability and application of study results to practice. Data will also be collected on any interventions applied between recruitment and outcome onset that may modify the outcome.

We will choose the candidate predictors a priori to be considered in the prediction model, based on the most promising predictor variables as identified with our previous systematic review [17–22]. The full list of variables to be evaluated for prediction of maternal and fetal outcomes is provided in Table 2.

**Table 2 Tab2:** List of candidate predictor variables to be evaluated in the PREP study

Maternal characteristics Maternal age at diagnosis (years) Gestational age at diagnosis (weeks) Number of fetuses in pregnancy at time of consent (1, 2, 3)
History Summary score for medical history—1 point for each of the following: pre-existing hypertension, renal disease, diabetes mellitus, autoimmune disease, previous history of pre-eclampsia (0, 1, 2 or more)
Symptoms Headache and/or visual disturbance (yes/no) Epigastric pain, nausea and/or vomiting (yes/no) Chest pain and dyspnoea (yes/no)
Bedside examination and tests Systolic blood pressure (mmHg, highest measurement over 6 h) Diastolic blood pressure (mmHg, highest measurement over 6 h) Clonus (yes/no) Exaggerated tendon reflexes (yes/no) Abnormal oxygen saturation (<95% on air) (yes/no) Urine dipstick (0, 1+, 2+, 3+, 4+ or more)
Laboratory tests Haemoglobin (g/L) Platelet count (× 10^9^/L) ALT (IU/L) Serum uric acid (μmol/L) Serum urea (mmol/L) Serum creatinine (μmol/L) Urine protein-creatinine ratio (PCR) (mg/mmol)
Management at baseline Administration of oral and/or parenteral anti-hypertensives (ongoing or commenced within 1 day of diagnosis) (yes/no) Administration of magnesium sulphate (commenced before or within 1 day of diagnosis) (yes/no)
Additional factors for fetal model only Uterine artery Doppler (normal/abnormal) Liquor volume (normal/abnormal) CTG findings (normal/abnormal) Estimated fetal weight <10th centile (yes/no)

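### The exclusion stops at outcomes before testing, so one baseline creatinine value can be both a predictor and a primary-outcome event

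*Protocol article*

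**What the plan says.** The Exclusion criteria section removes women if "any of the outcomes (including recurrent eclamptic seizures) occurs prior to testing". It does not mention an outcome that the baseline test itself reveals.

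Table 3 (Outcome measures) defines acute renal insufficiency by a creatinine threshold: "For women with an underlying history of renal disease: defined as creatinine >200 μM", and "for patients with no underlying renal disease: defined as creatinine >150 μM". It requires no rise, no new onset and no sample later than baseline.

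Table 2 (Candidate variables for inclusion in the model) lists serum creatinine among the laboratory tests. It is one of the 22 maternal candidate predictors (3 + 1 + 3 + 6 + 7 + 2 by block). The Model development section keeps continuous variables continuous.

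The Statistical analysis section measures time from diagnosis and also speaks of 48 h after admission. The survival failure event is bounded above at 34 weeks, and no lower bound tied to the baseline tests is given.

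**The concern.** The model is meant to forecast complications by 48 h and by discharge. A woman whose baseline creatinine is 180 μM, with no renal disease and no previous qualifying value, has had no recorded outcome before testing, so the literal rule lets her in. The 180 is then entered as her predictor value and also satisfies a component of the primary outcome. That event has been diagnosed at baseline, not predicted.

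Such women can steepen the creatinine coefficient and raise the apparent C-statistic. The planned bootstrap repeats variable selection in resamples that all carry the same definition, so the overlap is present in each one and the optimism estimate does not detect it. External validation would not expose it either if the same definitions are applied there, and Table 3 is itself adapted from one of the two validation studies. The two models may also treat these women differently: an event at the time origin adds no follow-up to the survival model but counts fully in the logistic model.

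**Working it through.** **Does anything else in the article close the gap?**
- The Candidate variables section refers to interventions between recruitment and outcome onset. That describes data collection and is not an eligibility or outcome rule.
- The failure event has an upper time limit only.
- Testing is not one moment: blood pressure is the highest reading over 6 h, and treatment predictors extend to 1 day after diagnosis.

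None of these says how an outcome first shown by the baseline sample is handled.

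**Which components are affected?**
- Creatinine: the same measurement is predictor and outcome, and the level alone suffices. The overlap is complete.
- Oxygen saturation: the predictor is below 95% on air. Pulmonary oedema uses below 94%, but also needs "Clinical diagnosis with x-ray confirmation or requirement of diuretic treatment". The overlap is partial.
- INR: it is not a candidate predictor, and the outcome must indicate DIC, which Table 3 says needs abnormal bleeding as well as consumptive coagulopathy. No predictor value is the event.

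**The article's own figure.** Sample size section: 10 predictors × 10 events per predictor / 0.20 = 500 women, that is 100 events. This reproduces, and the present point does not alter it.

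**Illustration of size.** Inputs:
- p, the share of women positive on the baseline creatinine: 1%, 2%, 3% (assumed; the article gives none).
- r, the event rate in the other women: 20% (the article's expected rate by discharge, set before delivery was added to the composite), or 50% (assumed, to represent the composite with delivery before 34 weeks).
- True C in the other women: 0.70 (assumed).
- Baseline-positive women are ranked above every non-event (assumed; this is the upper end).

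Share of events already present at baseline: w = p / [r(1 − p) + p]. Apparent C = w × 1 + (1 − w) × 0.70 = 0.70 + 0.30w.

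| r | p | w | C |
|---|---|---|---|
| 20% | 1% | 0.01/0.208 = 4.8% | 0.714 |
| 20% | 2% | 0.02/0.216 = 9.3% | 0.728 |
| 20% | 3% | 0.03/0.224 = 13.4% | 0.740 |
| 50% | 1% | 0.01/0.505 = 2.0% | 0.706 |
| 50% | 2% | 0.02/0.510 = 3.9% | 0.712 |
| 50% | 3% | 0.03/0.515 = 5.8% | 0.717 |

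If 20% and 50% are instead taken as overall rates, w = p/0.20 or p/0.50. C is then 0.715 to 0.745 (w 5% to 15%) or 0.706 to 0.718 (w 2% to 6%), much the same. The pairwise formula fits the AUC of the logistic model. For Harrell's C it is only a guide.

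**The case against.** The strongest reply is that a blood test detects raised creatinine and does not cause it. The condition existed before the sample was drawn, so a site could exclude the woman under the present wording, and the intent is evidently to remove women who already have an outcome. This is fair, and the article nowhere says that such women are enrolled. But the wording leaves it to each site to decide, so centres can apply the rule differently. The proposed change completes the same intent.

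A second reply is that a condensed article leaves operational detail to the full protocol. That would cover silence. Here the article states an eligibility rule and an outcome definition, and together they permit the overlap.

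A third reply is that the effect is small, since creatinine is one of 18 components and delivery before 34 weeks adds many events. This stands. Some baseline-positive women would also become events later through delivery, which shrinks the effect further.

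Three stronger readings are tempting, and the documents do not support them:
- That DIC and pulmonary oedema share the defect to the same degree. They do not, because each needs criteria beyond a baseline value.
- That a woman with renal disease and a known stable creatinine above 200 μM is swept in. If a previous value was above 200, the definition was met before testing and the existing exclusion arguably removes her.
- That a large share of events, with a C near 0.8, is an artefact. That needs a complications-only 48 h endpoint with a low event rate. The article does say the event rate ran below prediction, but no planned model uses that endpoint, because delivery before 34 weeks is now part of the outcome.

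**Conclusion.** The point holds for creatinine. On the stated rules, a woman whose first qualifying value is the baseline sample is not clearly excluded, and that value can count as predictor and event in the primary analysis. The planned internal validation cannot correct for this.

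The number of women affected cannot be derived from the article. Under the upper-end assumptions shown, C rises from 0.70 by about 0.014 to 0.040 at a 20% event rate, and by about 0.006 to 0.017 at an assumed 50%. The second range is nearer to the composite as now defined, if delivery before 34 weeks is common. The bias is therefore modest and runs towards optimism. It is worth correcting because the correction is cheap and no later step in the plan would reveal it.

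**What to change.** - Reword the exclusion to cover any outcome present before, or on the results of, the baseline assessment, and state what period that assessment spans.
- Count creatinine-defined renal insufficiency only from a sample taken after the baseline sample.
- Apply the same rule to women already recruited by removing those affected from the development set, and to the two external cohorts where their data allow.
- Report how many women are affected in each dataset.

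The cost is one or two sentences in the eligibility and analysis rules, applied to data already held, since the predictors are routine tests. The downside is the loss of a few events (under the illustration, about 5 to 13 per 100 at a 20% rate and 2 to 6 per 100 at 50%) and a slightly lower apparent C-statistic.
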